### Randomization, allocation and blinding

If all inclusion criteria are fulfilled and if the presence of UUI is determined, the participants will be randomly assigned to receive: (1) Transcutaneous Tibial Nerve Stimulation—Low Frequency (TTNS–LF), (2) Transcutaneous Tibial Nerve Stimulation—High Frequency (TTNS–HF), (3) Aussie Median Frequency (AMF), (4) Interferencial Median Frequency (IMF) and (5) High Voltage Stimulation (HVS). To ensure homogeneous distribution between groups, the participants will be randomly allocated to five therapeutic arms using permuted, block-randomization to balance the number of participants allocated to each group. The permuted block (with 15 participants per block) randomization sequence will be done through the website www.sealedenvelope.com by another physiotherapist unrelated to assessment process. After the assessment and randomization the participants will be schedule to the treatment sessions and will be informed about which group was allocated, but the difference between the groups will not be mentioned. All participants will be advised not to disclose to the assessor any details about the intervention program that they have received (to ensure that allocation is concealed from the assessor).

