### Eligibility criteria

#### Inclusion and exclusion criteria

Potential participants will be eligible for the study if they are between 18 to 80 years old with complaints of UUI. Potential participants will be ineligible for the study if they have cognitive impairment, psychiatric disorders, pregnancy, diagnosis of neurogenic bladder, pelvic organ prolapse greater than grade II, ongoing signs and symptoms of urinary tract infections, use of anticholinergic drugs, antagonists calcium, beta-antagonists, and dopamine antagonists, cannot commit to participating for the duration of treatment and those who do not sign the consent form.

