### Sample size and power analysis

A priori sample size calculation was performed using the G* Power 3.1 software. As the innovative comparisons methodology of this trial did not allow us to state our sample calculation on literature data, we calculated our sample size, based on F tests, ANOVA: repeated measures, within-between interactions, an effect size f of 0.17 were calculated considering a direct method using a small partial eta square (*n*^2^) of 0.03. Considering that we selected 5 therapies with potential treatment effects and we expect minimal differences between them, we considered the small effect size calculated by this appropriated method. In addition, we selected a power of 0.85, α error probability of 0.05, number of groups 5, number of measures 3, correlation among repeated measures of 0.5 and nonsphericity correction of 1 and a 10% dropout rate which estimated the recruitment of 105 participants, 21 per group.

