### Interventions

The intervention will be performed during 20 sessions of 45-minutes, twice a week for 10 weeks. All participants will carry out the treatment in groups of maximum 5 participants in the same room. They will remain seated comfortably during the entire treatment session. All participants will have their tibial nerve stimulated, with the current intensity adjusted to the highest possible sensory level, modified according to their habituation to the current, without reaching the motor threshold or causing pain [21].

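### A single fixed, published block size of 15 makes some allocations predictable to anyone at the site who knows the earlier ones, and concealment is stated only towards the assessor

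*Protocol article*

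**What the plan says.** Under Randomization, allocation and blinding, the article says that "the participants will be randomly allocated to five therapeutic arms using permuted, block-randomization to balance the number of participants allocated to each group". It fixes one size: "The permuted block (with 15 participants per block) randomization sequence will be done through the website www.sealedenvelope.com by another physiotherapist unrelated to assessment process". The Sample size section sets the target, "which estimated the recruitment of 105 participants, 21 per group". Recruitment is from one centre's waiting list, and no stratification factor is named, so this reads as one running sequence.

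The Design section limits blinding to the outcome assessor and the statistician. Women are told their group after randomisation and asked not to tell the assessor; the stated purpose is "to ensure that allocation is concealed from the assessor". The Interventions section adds: "All participants will carry out the treatment in groups of maximum 5 participants in the same room". The Currents section gives AMF and IMF each their own device and lists one common device for TTNS-LF, TTNS-HF and HVS. Electrode placement gives HVS an extra dispersive electrode.

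On who randomises, the sections disagree. Physiotherapeutic evaluation keeps both assessors out of screening, randomisation and treatment. The randomisation section gives the sequence to a physiotherapist separate from assessment. The Discussion says that a blinded assessor randomises the participants.

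**The concern.** In a permuted block of known size, the places left for each arm follow by subtraction from the places already used. Someone who knows the size and the earlier allocations can rule out arms late in the block and always knows the last one. Blinding the outcome assessor does not help here, because the risk arises at enrolment.

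The stake is selection bias at entry. Some entry criteria call for judgement, such as excluding a woman who "cannot commit to participating for the duration of treatment", and a waiting list leaves room to bring someone forward or hold her back. The Background states an expected direction, favouring medium-frequency currents. The sample size section expects only minimal differences between therapies, with 21 women per arm, so a small imbalance in prognosis could matter. Blinded measurement cannot repair such an imbalance.

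**Working it through.** **Inputs.** Block size 15, five arms with equal allocation (Randomization section); 105 women, 21 per arm (Sample size section). The observer is assumed to know the block size and every earlier allocation in order.

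**The plan's own figures.**
- 105 / 15 = 7 complete blocks; 15 / 5 = 3 places per arm per block; 7 × 3 = 21 per arm. The block design fits the target.
- The target reproduces from the unrounded effect size: f = √(0.03/0.97) = 0.1759 gives N = 95 (power 0.853), and 95 × 1.10 = 104.5, so 105. Nothing below depends on f.

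**Certain allocations.** An allocation is certain when all remaining places in the block belong to one arm.
- Slot 15: always.
- Slot 14: the last two places are the same arm, probability 2/14 = 0.143.
- Slot 13: the last three are the same arm, probability (2/14) × (1/13) = 0.011.
- Sum: 1 + 0.143 + 0.011 = 1.154 per block, which equals 15/13. Over 7 blocks: 8.1 of 105 (7.7%).

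**Narrowed allocations.** An exact recursion over all states of a block gives:
- at most two arms open: 2.538 per block × 7 = 17.8 (16.9%);
- at least one arm excluded: 6.989 per block × 7 = 48.9 (46.6%). From slot 12 on, this is unavoidable, because at most four places remain for five arms.

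**Best guess.** The probability of naming the next arm correctly is the largest remaining count divided by the places left. Its average is 0.20 at slot 1, 0.37 at slot 10, 0.47 at slot 13, 0.57 at slot 14 and 1.00 at slot 15. The sum over a block is 5.681, and 5.681 / 15 = 37.9%, against 1/5 = 20% by chance.

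**Alternatives, same observer** (for varied blocks, the observer knows the possible sizes but not the realised ones):

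| Scheme | Certain, of 105 | Best guess correct |
|---|---|---|
| Fixed blocks of 15 | 8.1 | 37.9% |
| Random 10/15/20, realised sizes unknown | about 2.2 | about 37.2% |
| Random 5/10/15, realised sizes unknown | about 3.3 | about 39.8% |
| One list of 105, 21 per arm | about 1.2 | about 27.7% |
| Earlier allocations not known | 0 | 20% |

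The varied-block rows are simulated. So is the single-list row; its certain count agrees with the closed form 105 / (105 − 21 + 1) = 1.24. Varying the size mainly removes certainty about block ends and hardly changes average guessing. Including blocks of 5 does not lower the guess rate.

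**The case against.** A reader might infer that earlier allocations are openly visible to the staff who screen, that nothing is concealed from them, and that all five currents run side by side in one session. The article does not support this. It does not say who screens, whether they treat, or what they see; it says only that the two assessors do not screen. It gives a shared room and a maximum group size, but does not say that a session mixes arms or that screeners attend. Three arms use the same device, so an onlooker might not tell TTNS-LF from TTNS-HF. Every predictability figure is therefore conditional on an assumed observer.

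Two further points also stand. Custody and release of the list may be set out in a full protocol that is not shown, so silence on them is not itself an error. The article already places randomisation after eligibility is established and refers to scheduling after assessment, which is part of the usual safeguard.

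Fifteen is also a fairly large block for five arms: blocks of 5 would make 21 of 105 certain. The count of 49 is generous too, because it includes cases where four arms remain open.

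These points limit the size of the concern without removing it. The fixed size is stated and printed, blinding is limited to two roles, and the only concealment purpose given concerns the assessor. The disagreement over who randomises is in the text whatever the screeners see.

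**Conclusion.** The concern holds as a modest, conditional weakness. If enrolling staff know the block size and the running history, about 8 of 105 allocations are certain, about 18 are down to two arms or fewer, and guessing succeeds 38% of the time instead of 20%. If they do not know the history, the fixed block leaks nothing. Steering of enrolment is a possibility that the design leaves open; the article neither states nor implies that it will happen. The sample size is unaffected. Separately, the Discussion's statement that a blinded assessor randomises conflicts with Physiotherapeutic evaluation and does not fit the Randomization section, so the article's account of who controls allocation is inconsistent.

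**What to change.** 1. Under Randomization, allocation and blinding, replace the fixed block of 15 by sizes drawn at random, for example from 10, 15 and 20, and do not disclose the sizes to site staff. If balance over calendar time is not a concern, one permuted list of 105 with 21 per arm lowers predictability further.
2. State that each allocation is released one at a time, after eligibility and baseline are recorded, by someone who neither screens nor treats. If a fuller document already provides this, a sentence saying so is enough. Keeping earlier and upcoming allocations from enrolling staff does more than any choice of block size.
3. Reconcile the Discussion with Physiotherapeutic evaluation and the Randomization section on who generates the sequence and who assigns participants.

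The cost is a new list and a few sentences. Varied blocks can leave the arms slightly uneven if recruitment stops mid-block; a single list gives weaker balance over time. If enrolment has begun, the change can apply only to the remaining allocations.

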### Interventions

The intervention will be performed during 20 sessions of 45-minutes, twice a week for 10 weeks. All participants will carry out the treatment in groups of maximum 5 participants in the same room. They will remain seated comfortably during the entire treatment session. All participants will have their tibial nerve stimulated, with the current intensity adjusted to the highest possible sensory level, modified according to their habituation to the current, without reaching the motor threshold or causing pain [21].

### Currents

○ **TTNS-LF:** Symmetrical biphasic pulsed current with 10Hz frequency, a pulse width of 200μs [6]. (Neurodyn Portable Ibramed^®^)○ **TTNS-HF:** Symmetrical biphasic pulsed current with 150Hz frequency, 100μs pulse width [10] (Neurodyn Portable Ibramed^®^).○ **AMF:** Medium frequency sinusoidal alternating current, with 4kHz carrier frequency and 4ms bursts with 100Hz frequency [20] (Aussie Sport Ibramed^®^).○ **IMF:** Biphasic pulsed current of medium frequency, with 4kHz with a modulated frequency of 100Hz and a with sweep of 10Hz [10] (Neurovector Ibramed^®^).○ **HVS**: Single-phase pulsed current, with triangular (exponential) twin pulses, frequency of 100Hz [11]. For this study, cathodic stimulation (negative pole) will be used (Neurodyn Portable Ibramed®).

### Electrode placement

For all groups, the current will be applied through a channel with two electrodes, one positioned posterior to the medial malleolus and the other 10 cm above. Uniform and rectangular silicone-carbon electrodes with 6x4.5 centimeters will be used. In addition, water-based gel will be applied as interface with the skin (Fig 3) [21].

**Fig 3 pone.0276722.g003:**
[figure not shown]
Electrode placement.

Before placing the electrodes, the skin will be cleaned with 70% alcohol. All groups will receive transcutaneous electrical stimulation through the tibial nerve for 30 minutes. However, on the high voltage group a third dispersive electrode of 13x9 centimeters will be positioned above the popliteal fossa to ensure the direction of the electrical current from tibial nerve directed to the sciatic nerve (Fig 4).

**Fig 4 pone.0276722.g004:**
[figure not shown]
Positioning of the dispersive electrode.

### Outcome measures

#### Primary outcome measure

The primary outcomes will be: 1) UI severity and 2) quality of life.

1) ISI is a validated questionnaire to Portuguese, that classify UI according to severity by multiplying two simple and brief questions about incontinence frequency and volume. The severity score is stratified into mild (one to two points), moderate (three to six points), severe (eight to nine), or very severe (total of 12 points) [19]. The ISI questionnaire will be applied in all time-points.1) Voiding diary is a self-real-life-assessment of voiding habits [22]. The 24-hour voiding diary shows greater acceptance by patients, but three-day voiding diary seems to be more suitable for possible evaluative interpretations [3]. The participants will fulfill during entire 3-days (72h) detailed information (including time of the event) about fluid intake (quantity), voiding (volume for each), leakage (time and associated reasons) and pad changes [22]. The voiding diary will be applied in all time-points.2) The ICIQ-SF is a brief self-administered questionnaire combined severity and bother-score through 4 questions about incontinence frequency, volume, impact of UI in daily life and self-diagnosis questions about mechanism reasons. The higher the score obtained is, the worse the quality of life related to that domain is [16]. The ICIQ-SF questionnaire will be applied in all time-points.2) The OAB-V8 will be used to assess the impact of overactivity bladder symptoms on quality of life. It is a questionnaire composed of 8 questions about the discomfort caused by the symptoms. The responses range from 0 to 5 points and in the sum of the results, if the total is ≥ 8, it will be considered as a probable diagnosis for UUI [17]. The OAB-V8 questionnaire will be applied in all time-points.2) The ICIQ-OAB questionnaire provides an assessment measure for voiding frequency, urgency, nocturia, and UI. It is composed of six specific questions about voiding symptoms correlating with quality of life, and the higher the score the worst the impairment [18]. The ICIQ-OAB questionnaire will be applied in all time-points.

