### Statistical analysis

The study will be run as a superiority trial. The statistical analysis will follow the per-treatment concept. Statistical analysis will be performed using SPSS software version 24.0 for Windows (IBM Corp., Armonk, N.Y., USA). The variables will be described by the mean and 95% confidence interval (95% CI). The distribution of normality will be analysed by the Shapiro-Wilk test. To analyse the effect of group and currents, ANOVA for repeated measures will be performed. The Mauchly’s test will be performed to test the hypothesis of sphericity and when if this violated the hypotheses, the analyses will be based on the Greenhouse-Geisser test. Peer-to-peer comparisons will be performed using the Bonferroni Post-Hoc test. The significant level adopted will be 5% (p ≤ 0.05).

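### Five unranked primary instruments share one undivided 5% level, so if a positive result on any one counts as success, the false-positive risk for the primary claim is well above 5%

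*Protocol article*

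**What the plan says.** In the protocol article, the section Primary outcome measure opens with "The primary outcomes will be: 1) UI severity and 2) quality of life". It then describes five instruments, numbered to match the two constructs:

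- **Severity:** the ISI ("The ISI questionnaire will be applied in all time-points") and a three-day voiding diary ("The voiding diary will be applied in all time-points"). The diary records fluid intake, voids, leakage and pad changes; none of these is named as the endpoint.
- **Quality of life:** ICIQ-SF ("The ICIQ-SF questionnaire will be applied in all time-points"), OAB-V8 ("The OAB-V8 questionnaire will be applied in all time-points") and ICIQ-OAB ("The ICIQ-OAB questionnaire will be applied in all time-points").

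No instrument is placed above another. The section Secondary outcome measure allows a single secondary outcome, pelvic floor muscle strength, so none of the five can be read as secondary.

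The Statistical analysis section declares a superiority trial, plans repeated-measures ANOVA, and says "The significant level adopted will be 5" (per cent). Its one multiplicity step is a Bonferroni post hoc test for pairwise comparisons. The section Sample size and power analysis rests on one group-by-time interaction test at alpha 0.05 and does not say for which instrument.

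**The concern.** Bonferroni on the pairwise comparisons guards against multiple contrasts within one ANOVA. It does nothing about running that ANOVA on five primary instruments, each at the full 5%. As written, a superiority claim could rest on whichever instrument crosses the threshold. If the instruments disagree, the protocol gives no way to say what the primary result is.

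The boundary between the two constructs is also blurred. ICIQ-SF is listed under quality of life, yet the text says "The ICIQ-SF is a brief self-administered questionnaire combined severity and bother-score through 4 questions", so it measures part of the severity construct as well.

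This matters more here than in many trials, because the sample size section expects only small differences between five active treatments. When true effects are small, a free choice among five instruments is more likely to produce a chance finding.

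**Working it through.** **1. Reproduce the plan's sample size.** Inputs from Sample size and power analysis: partial eta squared 0.03, alpha 0.05, power 0.85, k = 5 groups, m = 3 measures, correlation among repeated measures 0.5, nonsphericity correction 1, dropout 10%.

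- Effect size: f = sqrt(0.03/0.97) = 0.1759 (the article prints 0.17).
- Noncentrality: f² × N × m/(1 − 0.5). At N = 95: 0.03093 × 95 × 3/0.5 = 17.6.
- Degrees of freedom: (5 − 1)(3 − 1) = 8 and (95 − 5)(3 − 1) = 180.
- Power at N = 95: 85.3%.
- Dropout: 95 × 1.1 = 104.5, or 105; 95/0.9 = 105.6, or 106.

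The stated 105 is therefore reproduced as the size for **one** interaction test at 5%, using the unrounded f. With f = 0.17, power at 95 would be 82.3%.

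**2. Error rate for five tests at 5%, no true effect on any instrument, any one positive counted as success.**

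- Independent instruments: 1 − 0.95⁵ = 1 − 0.774 = 22.6%.
- Correlated instruments: the article gives no between-instrument correlation, so a range is assumed. The planned interaction F test (8 and 180 df, 95 completers) was simulated with a common correlation. Two separate runs gave:

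| Assumed correlation | At least one p < 0.05 |
|---|---|
| 0 | 22.7% to 22.8% |
| 0.3 | 21.4% to 21.5% |
| 0.5 | 19.3% to 19.4% |
| 0.7 | 15.6% to 15.9% |
| 0.8 | 13.7% to 13.9% |
| 0.9 | 10.3% to 11.0% |

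Even at 0.9 the rate is about twice the nominal 5%.

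**3. Two tests only, one per construct, each at 5%.** If independent: 1 − 0.95² = 9.75%. Reading the plan as two primary outcomes reduces the inflation but does not remove it.

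**4. What control costs, for the planned interaction test (f = 0.1759).** Recruitment is evaluable/0.9.

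| Alpha for the test | Power at 95 evaluable | Evaluable for 85% | Recruited |
|---|---|---|---|
| 0.05 (one primary) | 85.3% | 95 | 105 as stated |
| 0.025 (first Holm step, two primaries) | 77.7% | about 110 | about 123 |
| 0.01 (first Holm step, five primaries) | 66.5% | about 130 | about 145 |

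With f = 0.17, the powers at 95 evaluable are 82.3%, 73.9% and 61.9%.

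**The case against.** **The inflated figure depends on a success rule that the article does not state.** This is correct. If all five instruments had to be positive, an overall success claim would not be inflated. But no such rule is given either, and with each primary instrument tested at 5%, nothing in the text stops one positive result from being claimed. The figures must be given as conditional.

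**Independence is the least plausible case.** Also correct: these are patient-reported measures of overlapping symptoms. The 22.6% is the figure for independent tests and not a best estimate. A reader might infer a fixed error rate such as 14% to 23%. The article does not support that, because the lower end simply reflects stopping at a correlation of about 0.8; at 0.9 the rate is 10% to 11%.

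**The count of tests could be stretched too far.** A reader might infer that three assessment times and several diary recordings multiply the tests further. One interaction test covers all three times, and the article never says that each diary recording will be tested separately. What stands is narrower: no diary variable is named.

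**Multiplicity rules are often left to the analysis plan, and this is a condensed article.** That would excuse silence. Here the article itself makes five instruments primary, leaves one secondary outcome and fixes an undivided 5%. The point concerns what is stated.

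**Conclusion.** The concern holds in conditional form. The article fixes five primary instruments without ranking, tests at an undivided 5%, and adjusts only for pairwise arm comparisons. If a positive result on any one instrument is taken as success, the chance of at least one false-positive primary omnibus result is 22.6% under independence, and about 10% to 21% for assumed correlations from 0.9 down to 0.3.

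This assumes one omnibus test per instrument, no true effect on any of them, about 95 completers, and a common correlation that the article does not supply. The conclusion that the rate exceeds 5% does not depend on where in that range the correlation lies; the exact figure does.

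A reader might also infer that the repair is purely a matter of wording. It is so only with a single primary instrument. With more than one, the planned test loses power.

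**What to change.** Amend the protocol before unblinding, in one of two ways.

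- **Preferred: one primary instrument.** Analyse it by the planned three-time-point group-by-time interaction at 5%, and make the other four secondary. The stated 105 participants and 85% power then stand. The cost is that four instruments lose primary status.
- **Alternative: one instrument per construct.** Test the two by Holm: the smaller p-value at 0.025, then the other at 0.05. Three instruments become secondary and the power must be restated. At 95 evaluable, power for the first step falls from about 85% to 78%; restoring 85% needs about 110 evaluable, about 123 recruited.

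Holm across all five would control the error, but it starts at 0.01 with about 66% power (about 145 recruited to restore 85%). Reducing the number of primaries is the better choice.

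The sponsor should choose the instruments on clinical and measurement grounds; the statistics do not favour a particular one. If the diary is chosen, the single variable to be analysed must be named. The primary analysis should not be moved to a single week-10 comparison without redoing the sample size, which rests on the three-measure interaction.
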